## Abstract

**Background:**

Despite proven benefits through the secondary prevention of cardiovascular disease (CVD) and reduction of mortality, cardiac rehabilitation (CR) remains underutilized in cardiac patients. Underserved populations most affected by CVD including rural residents, low socioeconomic status patients, and racial/ethnic minorities have the lowest participation rates due to access barriers. Internet-and mobile-based lifestyle interventions have emerged as potential modalities to complement and increase accessibility to CR. An outpatient CR program using virtual world technology may provide an effective alternative to conventional CR by overcoming patient access limitations such as geographics, work schedule constraints, and transportation.

**Objective:**

The objective of this paper is to describe the research protocol of a two-phased, pilot study that will assess the feasibility (Phase 1) and comparative effectiveness (Phase 2) of a virtual world-based (Second Life) CR program as an extension of a conventional CR program in achieving healthy behavioral change among post-acute coronary syndrome (ACS) and post-percutaneous coronary intervention (PCI) patients. We hypothesize that virtual world CR users will improve behaviors (physical activity, diet, and smoking) to a greater degree than conventional CR participants.

**Methods:**

In Phase 1, we will recruit at least 10 patients enrolled in outpatient CR who were recently hospitalized for an ACS (unstable angina, ST-segment elevation myocardial infarction, non-ST-segment elevation myocardial infarction) or who recently underwent elective PCI at Mayo Clinic Hospital, Rochester Campus in Rochester, MN with at least one modifiable, lifestyle risk factor target (sedentary lifestyle, unhealthy diet, and current smoking). Recruited patients will participate in a 12-week, virtual world health education program which will provide feedback on the feasibility, usability, and design of the intervention. During Phase 2, we will conduct a 2-arm, parallel group, single-center, randomized controlled trial (RCT). Patients will be randomized at a 1:1 ratio to adjunct virtual world-based CR with conventional CR or conventional CR only. The primary outcome is a composite including at least one of the following (1) at least 150 minutes of physical activity per week, (2) daily consumption of five or more fruits and vegetables, and (3) smoking cessation. Patients will be assessed at 3, 6, and 12 months.

**Results:**

The Phase 1 feasibility study is currently open for recruitment which will be followed by the Phase 2 RCT. The anticipated completion date for the study is May 2016.

**Conclusions:**

While research on the use of virtual world technology in health programs is in its infancy, it offers unique advantages over current Web-based health interventions including social interactivity and active learning. It also increases accessibility to vulnerable populations who have higher burdens of CVD. This study will yield results on the effectiveness of a virtual world-based CR program as an innovative platform to influence healthy lifestyle behavior and self-efficacy.

## Introduction

### Underutilization of Cardiac Rehabilitation

Coronary artery disease (CAD) has become a pandemic as the leading cause of death worldwide [1]. CAD accounts for over two-thirds of cardiac-related deaths in the US and is associated with significant morbidity [2]. According to the 2014 Heart Disease and Stroke Statistics, an estimated 635,000 Americans suffer from an acute coronary event per year with approximately 300,000 recurrent events in CAD survivors [1]. Targeting behavioral risk factors including poor nutrition, smoking, and physical inactivity as well as conditions such as hypertension, hyperlipidemia, diabetes, and obesity is of utmost importance in order to significantly reduce CAD-associated morbidity and mortality [3-6]. Cardiac rehabilitation (CR) is an essential component of the mainstay therapy for patients following an acute coronary syndrome (ACS), such as acute myocardial infarction, for facilitation of recovery and secondary prevention of further events [7]. Evidence has consistently demonstrated that the comprehensive focus of CR on healthy lifestyle change reduces all-cause and cardiac-related mortality [8-10], and improves exercise capacity, psychosocial well-being, and quality of life [5,11]. However, despite its proven benefits, CR is greatly underutilized, especially among groups that need it most such as ethnic minorities, rural residents, the elderly, and the economically disadvantaged [12,13]. Many of the cited barriers to participation are both personal and systems-related including employment/time conflicts, lack of transportation, geographical accessibility, and financial constraints [12-14].

### Call for Innovation

The American Heart Association (AHA) Presidential Advisory board has recently issued a call for innovative reengineering of the traditional CR model towards approaches to improve adherence and effectiveness in cardiac patients [15]. Novel methods for reaching underserved populations who have the highest prevalence of cardiovascular disease (CVD) are crucially needed to assist in alleviating the burden and disparities within these groups. More Americans are embracing the digital world, with many accessing the Internet for health-related information [16,17]. The use of technology to deliver personalized medicine through mobile and Internet-based interventions has shown promise in improving user’s knowledge, health behaviors, and clinical outcomes [18]. There is recent evidence to suggest the effectiveness of Internet-based CR, termed virtual CR or eRehabilitation through the provision of health promotion programs at the user’s convenience [19-24].

### Study Purpose

Virtual world technology has emerged as a potentially powerful tool for the delivery of lifestyle interventions in the management of chronic diseases including diabetes [25] and obesity [26]. Virtual world environments are unique from Internet-based applications in that they are inherently immersive, engaging, and allow for “real world” interaction though personalized avatars or online personas [27,28]. Users of virtual world are provided with a more synchronous experience allowing for collaborative and experiential learning, skill-building, and “what if” hypothetical scenarios; all core concepts of CR [27,28]. We propose the use of a virtual world interaction as an extension to traditional face-to-face CR as a means for overcoming barriers to CR participation, and for positively impacting cardiac risk factors given its affordances of accessibility, social interactivity, and self-motivation. This virtual world interaction approach could potentially assist in widening access to and participation in CR among the US population as a whole while narrowing the gap in exemplary health outcomes among underserved groups. Our pilot study consists of the following two phases: (1) feasibility and (2) a comparative effectiveness, randomized clinical trial of virtual world based adjunct CR against conventional CR.

## Methods

### Study Setting and Participants

We will recruit patients who were recently hospitalized for an ACS (unstable angina, ST-segment elevation myocardial infarction, non-ST-segment elevation myocardial infarction), or who recently underwent elective percutaneous coronary intervention (PCI) at Mayo Clinic Hospital, Rochester Campus in Rochester, MN with at least one modifiable, lifestyle risk factor target: sedentary lifestyle (<3 hours of physical activity per week), unhealthy diet (consumption of <5 servings of fruits and vegetables daily), and current smoking (>1 year). All patients must have regular high-speed Internet access (either home, work, or community). Patient exclusion criteria will include less than 18 years of age, enrolled in a current CR program, and non-fluent in English. The feasibility research protocol was reviewed and approved by the Mayo Clinic Institutional Review Board and the randomized controlled trial (RCT) will be registered. We include details of the design and methods of both the feasibility study and the proposed RCT as Phases 1 and 2, respectively.

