#### Measures

The primary outcome is a composite including improvement of at least one of the following 3 cardiac risk factors at baseline, 3, 6, and 12 months (1) physical activity (at least 150 minutes per week), (2) diet (consumption of five or more fruits and vegetables daily), and (3) smoking (complete cessation for baseline smokers, maintained nonsmoking status for baseline nonsmokers). Secondary outcomes will include improvement in all 3 cardiac risk factors, intention and self efficacy to achieving lifestyle change [41,44,45], change in exercise capacity by peak oxygen uptake (VO_2_), change in weight (≥5% weight reduction for patients with baseline BMI >30 kg/m^2^), blood pressure optimization (blood pressure <140/90 mmHg, <130/80 mmHg for diabetics), diabetes control (hemoglobin A1c<7%), hyperlipidemia control (low-density lipoprotein <100 mg/dL), medication adherence [39], social support/influence [46], physical and mental health-related quality of life [47], heart disease knowledge [40], and user evaluation of the virtual world platform (satisfaction, usability, and utility) [22,35-38].

Physical activity will be assessed by the International Physical Activity Questionnaire (IPAQ) which determines physical activity patterns (vigorous-intensity, moderate-intensity, and leisure) over the previous seven days [43]. Furthermore, free-living physical activity data will be obtained from personal activity trackers as number of steps per day [48]. All patients will undergo a symptom-limited ETT with oxygen consumption testing to assess for peak VO_2_ [52,53]. Continuous blood pressure and heart rate measurements, as well as electrocardiograms will be obtained during exercise and recovery periods. A brief dietary recall by a food frequency questionnaire will allow for diet evaluation [42]. Mayo Clinic laboratories will process and analyze all fasting blood specimens including lipid panel (total cholesterol, triglycerides, high density lipoprotein cholesterol, and low density lipoprotein cholesterol), blood glucose, and hemoglobin A1c. Physical examination measures including height, weight, body mass index, waist circumference, and blood pressure will be obtained according to standard guidelines and Mayo Clinic protocols [54-55]. The baseline questionnaires and clinical assessments will be repeated at 3, 6, and 12 months (study completion).

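### The activity cut-off for entry (under 180 min/week) overlaps the success cut-off (150 min/week or more), and the composite does not restrict credit to factors deficient at baseline

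*Protocol article*

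**What the plan says.** **Entry.** Under Study Setting and Participants, the first two qualifying factors are "sedentary lifestyle (<3 hours of physical activity per week), unhealthy diet (consumption of <5 servings of fruits and vegetables daily"). The third is "current smoking (>1 year"). One factor suffices.

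**Outcome.** The Measures section of Phase 2 states: "The primary outcome is a composite including improvement of at least one of the following 3 cardiac risk factors at baseline, 3, 6, and 12", counted in months. The components are "physical activity (at least 150 minutes per week"), five or more fruits and vegetables a day, and a smoking component met by quitting or, for baseline nonsmokers, by remaining a nonsmoker. The Methods paragraph of the abstract gives the same composite as targets met, including "at least 150 minutes of physical activity per week", and does not use the word improvement.

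**Sample size.** Sample Size Estimation and Power Calculations assumes that 45% of control and 74% of intervention patients will have at least one behavioural risk factor corrected at 12 months. It asks for 50 per group for 80% power at alpha 0.05, and recruits 120 to allow for 10% drop-out.

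**The concern.** A deficiency used for entry and a target used for success should be complements on the same scale. For diet they are: fewer than five servings to enter, five or more to succeed. For activity they are not, and the two ranges overlap.

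Separately, entry requires one deficient factor and success requires one target met, but nothing says it must be the same factor, or one that was deficient at baseline. Someone enrolled for one factor may already be at target on another.

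What is at stake is the meaning of the primary outcome and its power. Patients who count as successes without changing add equally to both arms. They raise the control rate, shrink the absolute difference and move the trial away from the rates used to size it.

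**Working it through.** **1. The overlap.** 3 h × 60 = 180 min. Entry as sedentary: below 180 min/week. Success on activity: 150 min/week or more. Both hold from 150 to below 180, a window of 30 minutes.

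**2. Who can enter while already at an activity or diet target.**
- A patient at 150 to 179 min/week, enrolled as sedentary.
- A patient enrolled for diet alone who does 150 min/week or more.
- A patient enrolled for inactivity alone who already eats five or more servings a day.

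The last two would exist even if the activity cut-offs matched, because they arise from the any-one-factor rule.

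**3. The two readings of the outcome.**
- *Status reading (abstract).* All three types succeed without change if they stay where they are.
- *Change reading (improvement in Phase 2 Measures, correction in the sample size section).* They get no credit for a target already met. The patient at 150 to 179 min/week cannot newly reach the activity target, which is the factor that qualified that patient for entry.

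The cut-offs therefore conflict on either reading, though in different ways.

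**4. The plan's own figure.** For 45% versus 74%, two-sided 0.05, 80% power, the mean rate is 0.595:

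n = [1.96·√(2·0.595·0.405) + 0.842·√(0.45·0.55 + 0.74·0.26)]² / 0.29² ≈ 44 per arm, or 51 with continuity correction.

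Fisher's exact test at 50 per arm has 80.5% power. The stated 50 per group reproduces, for an outcome that is a correction.

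**5. Illustration under the status reading.** Let f be the share already at an activity or diet target who stay there in both arms, and let the rest succeed at 45% and 74%. The smoking component is left out. Then:

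- control rate = f + (1 − f)·0.45
- intervention rate = f + (1 − f)·0.74
- difference = 0.29·(1 − f)

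The number left after drop-out is 120 × 0.90 = 108, or 54 per arm. Exact power of the two-sided chi-square test:

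| f (assumed) | Control | Intervention | Difference (points) | Power, 50/arm | Power, 54/arm |
|---|---|---|---|---|---|
| 0 | 45.0% | 74.0% | 29.0 | 85.7% | 87.6% |
| 10% | 50.5% | 76.6% | 26.1 | 78.6% | 82.0% |
| 20% | 56.0% | 79.2% | 23.2 | 70.7% | 74.4% |
| 30% | 61.5% | 81.8% | 20.3 | 62.6% | 65.5% |

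The document gives no baseline distribution of activity or diet, so f is an assumption throughout. The table does not cover the change reading, where a blocked patient would lower the success rates instead of raising them.

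**The case against.** **The Methods text asks for improvement, the hypothesis speaks of improving behaviours, and the abstract is only a condensation.** This is the strongest defence against automatic success, and it has weight: a reader might infer that every patient already at target is counted as a success, and the document does not establish that. But the word improvement does not settle the matter. The same sentence credits baseline nonsmokers for staying nonsmokers, and the abstract omits the word.

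**On the change reading the harm is narrow.** This stands. A patient at 150 to 179 min/week may still succeed on diet, or on smoking if a smoker.

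**The power loss is not the effect of 180 versus 150.** This also stands. A reader might infer from the table that the cut-off mismatch alone costs 7 to 23 points of power. The document does not support that: f pools the 30-minute window with everyone who enters on a different factor, and nothing in the text sizes either group.

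**Recruitment has a margin.** At 54 per arm, power is still 82% at f = 10%. A fall below 80% needs a larger f, for which the document offers no evidence.

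**The maintained-nonsmoking clause matters more.** On a status reading it makes every baseline nonsmoker who stays one a success, so the activity overlap would then alter the result only for baseline smokers. The overlap is still a separate defect, because rewording the smoking clause alone would leave it in place.

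**Conclusion.** The point holds as an inconsistency between eligibility and endpoint. The activity cut-offs overlap by 30 minutes a week, and no text limits credit to a factor deficient at baseline, although the sample size is built on correction of a factor. This needs only the figures printed in the article.

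The consequence for power is illustrative. It rests on three assumptions: the status reading, an f the document does not give, and patients at target staying there in both arms. Across f of 10% to 30%, power is 79% to 63% at 50 per arm and 82% to 65.5% at 54 per arm. It would be wrong to conclude that the trial is shown to be underpowered or that the 180-versus-150 mismatch is the main cause; most of f may come from the any-one-factor rule. If only factors deficient at baseline count, f is zero and the stated 50 per group stands.

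This should be corrected before Phase 2 enrols, together with the maintained-nonsmoking clause.

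**What to change.** 1. In the abstract and in Phase 2 Measures, define success as reaching target at follow-up on at least one factor that was below target at the baseline visit. This also closes the maintained-nonsmoker route, so the two points should be handled in one edit. It brings the endpoint into line with the correction assumed in the sample size.

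2. Reconcile the activity cut-offs in Study Setting and Participants and Phase 2 Measures, so that deficient at entry is the exact complement of success. The document does not say which figure should give way; that choice belongs to the trial team.

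3. State that baseline deficiency for the endpoint is judged on the baseline-visit questionnaire. The activity questionnaire covers the previous seven days, and some patients are screened before dismissal from hospital; a recall taken then would include inpatient days and could class a usually active patient as deficient. The article does not give the interval from dismissal to the baseline visit, so the team should check that the seven days fall after dismissal.

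**Cost.** The endpoint change is wording and uses data already planned at baseline. If the entry cut-off is the one lowered, patients at 150 to 179 min/week with no other deficient factor become ineligible. A patient screened as deficient may also prove to be at target on every factor at the baseline visit, and the definition should say how such a patient is counted.

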### Phase 1: Feasibility Study

#### Hypothesis

We hypothesize that a virtual world-based CR program can be successfully implemented as an extension of a face-to-face conventional CR program. We plan to evaluate a priori how patients utilize a virtual world-based program for CR and secondary CVD prevention by conducting a 12-week feasibility study. Our goal is to apply the evaluation information obtained from Phase 1 towards the design of a patient-driven and centered virtual world platform prototype (*Destination Rehab*) with high usability, understandability, and credibility.

#### Recruitment

Eligible patients (approximately 10) will be invited to participate from the Mayo Clinic outpatient CR enrollment listings by the study cardiovascular nurse. Evidence supports that at least 5 participants are sufficient to assess usability of Web-based applications [29,30].

#### Intervention

We plan to hold a series of weekly, one-hour sessions over three months on a secure virtual world platform via an established Mayo Clinic infrastructure, Linden Lab’s Second Life, covering relevant cardiovascular health topics including CAD, hypertension, hyperlipidemia, and diabetes (see Textbox 1 and Figure 1) [31]. The sessions will be led by a cardiovascular diseases specialist and a cardiovascular nurse educator both trained in motivational interviewing and the Second Life application. Technical support staff will assist with any virtual world technology technical issues and troubleshooting. We will also hold live “ask-the-expert” group chat sessions on diet and exercise from a dietician and exercise physiologist, respectively. Participants will engage in virtual activities including grocery store and restaurant tours (to discuss healthy food choices, portion control, and nutrition label reading), as well as a variety of fitness activities (see Figures 2-4) [32-34]. Peer discussion forums will be available at all times to the participants. A few of our intervention preparation techniques were adapted from those endorsed by Rosal et al as established processes for virtual world interventions [25]. Participants will receive hands-on training and support including an overview of the virtual world platform, creating a Second Life account (including avatar), and navigation of the *Destination Rehab* prototype. Participants will also be provided with an instructional manual including step-by-step screen shots to support their independent home use. Upon training completion, participants will be provided with a personal laptop for use during the study, complete with required software to access the virtual-world platform and CR program materials, as well as a personal headset with microphone to facilitate communication in virtual world.

Comparison of virtual world adjunct versus conventional cardiac rehabilitation program curricula.Comparison of program curriculaVirtual worldManaging heart disease risk factors (hyperlipidemia, hypertension, diabetes, obesity, and tobacco use)Stress management and relaxation after cardiac events“Ask-the-expert” group chat sessions on nutrition and physical activity with dietician and exercise physiologistVirtual grocery store and interactive restaurant tour with dietician (selecting healthy foods, proper portion sizes, nutrition label reading, etc.)Medications after a cardiac eventSexuality after a cardiac eventPeer group “social hour” discussionsConventionalManaging heart disease risk factors (hyperlipidemia, hypertension, diabetes, obesity, and tobacco use)Stress management and relaxation after cardiac eventsDietician nutrition counseling (hints for grocery store shopping, dining out, healthy seasoning, etc.)Cooking demonstrationPhysical activity counseling with exercise physiologist (personalized exercise program/prescription)Medications after a cardiac eventSexuality after a cardiac eventSupport groups

**Figure 1 figure1:**
[figure not shown]
Mayo Clinic conference center virtual world platform in the Second Life application.

**Figure 2 figure2:**
[figure not shown]
Example of virtual grocery store tour.

**Figure 3 figure3:**
[figure not shown]
Example of interactive restaurant tour.

**Figure 4 figure4:**
[figure not shown]
Example of virtual fitness center.

#### Measures

We plan to evaluate utility and usability, as well as user satisfaction for each user. Application usage statistics for each participant will be collected to report the frequency and duration of each interaction with the virtual world platform. Furthermore, assessments of participant-to-participant and participant -to-speaker communication during sessions will allow for an appreciation of the participant's sense of immersion and engagement. Feedback on the site usability and utility will be measured by survey and interview consisting of questions from previously validated tools [22,35-38]. The usability questions will include participant impressions of the graphical interface, as well as opinions and attitudes towards the visual appeal (ie, application was designed with the user in mind), content (ie, information was complete), navigation (ie, steps required to complete a task were logical), informational architecture (ie, visual layouts were logical), and interactive features. User satisfaction will be assessed by open response questions to allow participants to provide feedback on likes, dislikes, or concerns about the virtual world platform, and sections to provide recommendations for changes to the program. At Phase 1 completion, study participants will complete a final evaluation survey assessing their willingness to use a similar virtual world platform for CR. Results of this formative evaluation process will inform changes and adjustments to our virtual world program for Phase 2.

